## Abstract

It has been previously demonstrated that ticagrelor can reduce mortality compared to clopidogrel in acute coronary syndrome (ACS) patients. However, the mechanism for this mortality reduction remains uncertain. The objective of the present study is to assess the impact of chronic ticagrelor treatment on microvascular circulation. A total of 120 participants aged 20–85 years with clinical diagnosis of ACS will be randomized in a 1:1 fashion to the following two groups: ticagrelor 90 mg twice daily; clopidogrel 75 mg once daily. To evaluate the status of microcirculation, the primary end point is coronary microvascular dysfunction measured using an index of microcirculatory resistance (IMR) at 6 months after receiving the study agent. The purpose of this trial is to investigate whether ticagrelor, beyond its antiplatelet efficacy, could improve coronary microcirculation more effectively than clopidogrel for patients with ACS.

## Background

Acute coronary syndrome (ACS) is a condition of suddenly reduced blood flow to the heart. Patients with ACS have elevated levels of platelet activity [1, 2]. They are at substantial increased risk for adverse cardiovascular events. Current treatment guidelines recommend antiplatelet therapy to reduce the risk of myocardial infarction, stroke, and cardiac death in patients with ACS [3, 4]. Ticagrelor is a reversible, potent, and oral adenosine diphosphate (ADP) P2Y12 receptor blocker developed as a treatment for patients with ACS. It has been demonstrated that ticagrelor can reduce the mortality of patients with ACS compared to clopidogrel from Platelet Inhibition and Patient Outcomes (PLATO) study [5]. However, the mechanism involved in its mortality reduction remains uncertain.

Several hypotheses have been suggested to explain the mechanism of the impressive benefit of ticagrelor beyond its antiplatelet action. One hypothesis is adenosine theory that some benefits of ticagrelor might be attributed to adenosine-medicated mechanism. Adenosine has been proposed to have cardioprotective effect as a physiologically potent vasodilator [6]. Several clinical studies support the hypothesis that adenosine could reduce cardiac ischaemia reperfusion damage [7, 8]. Ticagrelor can increase levels of extracellular adenosine by inhibiting adenosine reuptake [9, 10], leading to a significant increase in adenosine-induced coronary vasodilatory response [11]. Through these pathways, ticagrelor might be able to prevent microvascular dysfunction. A recent study has reported that in ST-segment elevation myocardial infarction (STEMI) patients, 180 mg loading dose of ticagrelor might be more effective in reducing microvascular injury than 600 mg loading dose of clopidogrel as demonstrated by an index of microcirculatory resistance (IMR) immediately after primary percutaneous coronary intervention (PCI) [12]. However, there are no available data on coronary microcirculation effects after chronic treatment of ticagrelor in patients with ACS who have altered resting coronary blood flow dynamics due to advanced coronary artery disease.

Therefore, the objective of this comparison trial of ticagrelor and clopidogrel on microcirculation in patients with ACS undergoing PCI is to determine whether ticagrelor might have potential benefit on coronary microcirculation in ACS patients undergoing PCI during 6 months follow-up period compared to clopidogrel.

## Methods/Design

### Study End Points

The primary hypothesis to be tested is whether ticagrelor could significantly improve coronary microcirculation in ACS patients undergoing PCI with 6 months of follow-up period compared to clopidogrel. To evaluate the status of microcirculation, the primary end point is coronary microvascular dysfunction measured using an IMR at 6 months after receiving the study agent. Secondary end points include fractional flow reserve (FFR), coronary flow reserve (CFR), and a change in IMR from randomization to the end of treatment using coronary pressure-temperature wire on culprit lesion during 6 months of follow-up.

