### Study Protocol

This trial is designed as a non-blinded, open label, parallel-group, prospective, and randomized controlled clinical trial performed in a single center. Written informed consent is obtained from each participant before diagnostic coronary angiogram and randomization. After baseline measurement, participants are randomly allocated into ticagrelor or clopidogrel group. All patients are pretreated with aspirin 300 mg orally and a loading dose of ticagrelor 180 mg or clopidogrel 600 mg according to the randomization. After PCI for index vessel, physiologic measures including FFR, CFR, and IMR are obtained twice (6 months apart) from the culprit artery after PCI. Patients will receive ticagrelor 90 mg twice daily or clopidogrel 75 mg once daily for at least 6 months. All patients in PLEIO trial are treated with rosuvastatin 5 mg (Crestor, AstraZeneca, Cambridge, UK) per day during the study period. Any patient who is found to take less than 80% or more than 120% of the assigned study drug is considered non-compliant as assessed by tablet counts [13]. All patients are advised to maintain aspirin (≥ 80 mg/day) lifelong. The trial is overseen by an independent data monitoring committee.

Recruitment of participants was started in December 2014. The total number of randomized subjects will be 120. Baseline characteristics of these patients enrolled in PLEIO are shown in Table 2. The process of the trial conduct is illustrated in Fig. 1. It was registered under www.clinicaltrials.gov: NCT02618733.

**Table 2 Tab2:** Clinical characteristics and treatment at baseline

	Ticagrelor (*n* = 60)	Clopidogrel (*n* = 60)	*p* value
Age	56.9 ± 11.4	58.5 ± 9.9	0.14
Male	46 (76.7%)	44 (73.3%)	0.69
Height (cm)	167.4 ± 8.1	165.5 ± 7.7	0.20
Weight (kg)	70.5 ± 12.8	66.4 ± 10.6	0.06
Risk factors			
Diabetes	21 (35.0%)	22 (36.7%)	0.50
Hypertension	27 (45.0%)	27 (45.0%)	0.57
Hypercholesterolemia	18 (30.0%)	17 (28.3%)	0.50
Current smoker	35 (59.3%)	35 (42.4%)	0.09
Ejection fraction (%)	52.0 ± 8.7	52.4 ± 8.9	0.81
Biomarker			
Serum hemoglobin (g/dL)	14.5 ± 1.7	14.0 ± 1.4	0.07
Platelet count (× 10^9^/L)	23.9 ± 5.5	22.9 ± 6.9	0.40
Serum creatinine (mg/dL)	1.0 ± 0.3	1.0 ± 0.2	0.15
HbA1c (%)	6.7 ± 1.7	6.3 ± 1.3	0.10
Lipid profile			
Total cholesterol	184.3 ± 45.1	195.8 ± 45.8	0.17
LDL cholesterol	119.5 ± 36.4	115.5 ± 32.3	0.53
HDL cholesterol	41.9 ± 9.2	44.1 ± 11.9	0.27
Triglycerides	182.5 ± 87.3	186.1 ± 72.8	0.23
Cardiac troponin-I	49.1 ± 58.9	39.9 ± 70.8	0.44

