### Coronary Intervention and Physiologic Measurements

PCI is performed according to the latest standard guidelines [14, 15]. All culprit lesions are treated with biodegradable polymer drug-eluting stent (Orsiro, Biotronik, Berlin, Germany). Angiographic success is defined as a residual stenosis ≤ 30% by visual analysis in the presence of Thrombolysis In Myocardial Infarction (TIMI) grade 3 flow.

Physiologic measurements are performed for the culprit vessel immediately and after 6 months after PCI. A six to seven French coronary guiding catheter without side-hole is used to engage the selected coronary artery. An intracoronary pressure and temperature sensor-tipped guidewire (PressureWire Certus, ST. Jude Medical, MN, USA) is used to measure distal coronary pressure. The index of coronary flow is derived from the coronary thermodilution method as described previously [16]. After the culprit lesion is successfully treated, the guidewire is calibrated for pressure recording. It is then equalized with aortic pressure in the guiding catheter after injection of 200 μg of intracoronary nitroglycerin. The tip pressure sensor is advanced across the stented segment and beyond the mid-to-distal portion of the culprit vessel. Aortic pressure (Pa) and distal intracoronary pressure (Pd) are obtained at baseline. FFR is calculated as the mean Pd divided by mean Pa during maximal hyperemia. To measure CFR, the coronary flow under basal conditions is determined by intracoronary administration of 3 mL of room temperature saline three times in succession (3 mL/s) manually. Maximal hyperemia is then induced, and three additional intracoronary room temperature saline boluses of 3 mL are administered to determine peak coronary flow presented as peak mean transit time (Tmn). CFR is calculated based on the ratio of mean transit times during hyperemia and at baseline. After evaluation of FFR and CFR, IMR is calculated. In culprit vessel, a simplified method of IMR is calculated as follows:$$ \mathrm{IMR}=\mathrm{Pd}\ \mathrm{during}\  \mathrm{maximal}\  \mathrm{hyperemia}\times \mathrm{Tmn} $$

To induce maximal hyperemia, intravenous adenosine is administered via the right femoral vein (140 mg/kg/min).

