### Platelet Function Measurements

Platelet function measurements are performed to assess platelet reactivity. Blood sample withdrawal for assessing platelet function is conducted at least 6 h after the loading dose of clopidogrel or 2 h after the loading dose of ticagrelor [17]. Blood samples are acquired via sheath in the catheterization laboratory prior to each physiologic measurement and collected in 3.2% citrate Vacuette tubes (Greiner Bio-One Vacuette North America, Inc., Monroe, NC, USA). Platelet reactivity is measured using VerifyNow P2Y12 assay (Accumetrics, San Diego, CA, USA). It is numerically expressed in P2Y12 reaction units (PRU). The time interval between blood sampling and VerifyNow P2Y12 testing does not exceed 2 h.

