### Statistical Analysis

Continuous data are analyzed using Student’s *t* test. Chi-squared test is used to analyze categorical variables. The focus of this trial is to compare the efficacy by measuring IMR between the two study groups. Statistical analyses are performed on an intention-to-treat basis. The two-sided null hypothesis for the primary end point states is that ticagrelor has potential benefit to improve coronary microcirculation in ACS patients undergoing PCI. Primary end point is assessed using Student’s *t* test if samples are normally distributed or their variances are homogeneous. Otherwise Mann-Whitney *U* test is used. Two-way analysis of variance (ANOVA) with repeated measures is used to detect changes in IMR values from randomization to the end of treatment in the two study groups. The operator’s reproducibility is evaluated by using both linear regression analysis and the Bland-Altman method to assess limits of agreement between repeated measurements.

Safety analysis includes calculation of frequencies and rates of bleeding reported in the two groups. This analysis is performed on the full analysis set which consisted of patients who received at least one dose of the study medication. Graphical methods including scatter plots and boxplots are used to visualize findings of the trial. The Kaplan-Meier method is used to plot the time to the first episode of cardiovascular events after PCI. Subgroup analyses will be performed to evaluate QOL among ACS patients. Difference in QOL between hospital admission and 6-month follow-up will be categorized as improvement in QOL when the difference is greater than zero or lack of improvement when the difference is less than zero. All statistical analyses are performed using SPSS version 16.0 or higher. Statistical significance is considered at *p* < 0.05.

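### The change in IMR is defined from randomization, but the first IMR is taken after the randomized loading dose and PCI, so this secondary end point cannot include any early drug effect

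*Protocol article*

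**What the plan says.** Under Study End Points, the protocol article names as a secondary end point "a change in IMR from randomization to the end of treatment using coronary pressure-temperature wire on culprit lesion". Under Statistical Analysis, a two-way repeated-measures ANOVA "is used to detect changes in IMR values from randomization to the end of treatment in the two study groups".

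The schedule is given in three other sections:

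- **Study Protocol.** Patients are pretreated with "a loading dose of ticagrelor 180 mg or clopidogrel 600 mg according to the randomization". Later in the same paragraph, "physiologic measures including FFR, CFR, and IMR are obtained twice (6 months apart) from the culprit artery after PCI".
- **Coronary Intervention and Physiologic Measurements.** "Physiologic measurements are performed for the culprit vessel immediately and after 6 months after PCI". The wire is prepared only once the stenting is done: "After the culprit lesion is successfully treated, the guidewire is calibrated for pressure recording".
- **Platelet Function Measurements.** Blood is drawn "at least 6 h after the loading dose of clopidogrel or 2 h after the loading dose of ticagrelor", and this sampling comes before each physiologic measurement.

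The Study Protocol section also says that allocation follows a baseline measurement, without saying what was measured. The primary end point is IMR at 6 months, which does not use the first IMR.

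**The concern.** A change from randomization needs a value that treatment has not yet touched. Here the first IMR comes after allocation, after the arm-specific loading dose and after PCI. It is an outcome on treatment.

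This goes beyond a loose label because of the trial's own rationale. The Background cites a STEMI study in which the same ticagrelor loading dose "might be more effective in reducing microvascular injury than 600 mg loading dose of clopidogrel", judged by IMR immediately after primary PCI. That is the moment of this trial's first IMR. Any benefit already present then is left out of the later change. A reader told that the change runs from randomization could take a small or null difference in change as absence of a drug effect, even beside a clear difference in 6-month IMR.

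**Working it through.** **1. Order of events.** The sections quoted above give: allocation, loading dose by arm, PCI, first IMR, then second IMR 6 months later. The platelet sampling rule confirms it. Blood is taken at least 2 h (ticagrelor) or 6 h (clopidogrel) after loading and before the physiologic measurement, so the first IMR follows the randomized drug by at least that long. No IMR at or before randomization is described.

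**2. What the change contrast estimates.** Let D1 be the between-arm difference at the first IMR and D6 the difference at 6 months.

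- Difference in change = D6 − D1. With two visits, the arm-by-time term of the ANOVA tests the same quantity.
- The arm main effect averages the visits, (D1 + D6)/2, so it does not subtract D1.
- The effect since randomization at 6 months is D6. The change contrast equals it only if D1 = 0.

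**3. Inputs for an illustration.**

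- From Sample Size: 35 U on clopidogrel and 25 U on ticagrelor, so D6 = 10 U; two-sided 5% level; 90% power; 20% loss; 60 per arm, so 60 × 0.8 = 48 evaluable per arm.
- Not in the article: the SD, the correlation ρ between the two IMRs, and D1. These are assumptions.

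**4. The plan's own figure.** No SD is stated, so 60 per arm cannot be reproduced independently. The SD it implies is

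SD = 10 × √(48/2) / (1.960 + 1.282) = 15.1 U.

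With that SD the formula returns 48 per arm, and 48/0.8 = 60. Power for 6-month IMR is then 90%, whatever D1 is. Using 30% of 35 U, which is 10.5 U, as the difference would imply an SD of 15.9 U.

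**5. Power of the change contrast.** SD of change = 15.1 × √(2(1 − ρ)): 17.9 U for ρ = 0.3, 15.1 U for 0.5 and 11.7 U for 0.7. Standard error = SD of change × √(2/48). By normal approximation, power is close to Φ[(D6 − D1)/SE − 1.96].

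| Early difference D1 | Difference in change | ρ = 0.3 | ρ = 0.5 | ρ = 0.7 |
|---|---|---|---|---|
| 0 U | 10 U | 78% | 90% | 99% |
| 2.5 U | 7.5 U | 54% | 68% | 88% |
| 5 U | 5 U | 28% | 37% | 55% |
| 7.5 U | 2.5 U | 10% | 12% | 18% |
| 10 U | 0 U | 5% | 5% | 5% |

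For example, with D1 = 5 U and ρ = 0.5, SE = 15.1 × √(2/48) = 3.08, 5/3.08 = 1.62, and Φ(1.62 − 1.96) = 37%.

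**The case against.** **The first IMR may be a true baseline.** Allocation is said to follow a baseline measurement. But that measurement is not called IMR. If IMR were meant, it would conflict with the same paragraph, which puts both IMR measurements after PCI, and with the two other sections on timing. The phrase is an ambiguity to reconcile and does not rescue the end point. The design figure, which might clarify it, is not shown.

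**The attenuation is conditional.** This stands. The cited evidence is tentative, gives no size in the article and concerns STEMI, which makes up 18 + 20 = 38 of 120 patients (32%) in Table 2. With no acute effect nothing is lost, although the name remains wrong. A reader might infer that the change analysis necessarily removes part of the drug effect; the documents support only that it would do so if an early difference exists.

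**Change from post-loading to 6 months is a sensible quantity.** This also stands. The stated objective is the effect of chronic treatment, and this change fits it. The fault is that it is presented as change from randomization.

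**Further readings that the documents do not support.** A reader might infer that the main result is compromised; the primary test and the sample size rest on 6-month IMR alone. A reader might also suppose that the first IMR serves as an adjustment covariate or as evidence of baseline balance; no such use is planned, and Table 2 does not list IMR. Nor is recovery after ACS a confounder of the arm comparison: recovery common to both arms cancels in the arm-by-time term, and efficacy is not said to rest on the time effect alone.

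**Conclusion.** The timing fault is established from the article's own text: the end point and the ANOVA are named as change from randomization, and the planned measurements cannot supply that. Any between-arm difference at the first IMR is removed one-for-one from the change score and from the arm-by-time term, though not from the arm main effect.

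How much this matters is unknown. The figure of about 28–55% power with an early 5 U difference is hypothetical: it rests on an SD solved back from the sample size, assumed correlations of 0.3–0.7 and an assumed early effect. The trial makes no power claim for this end point, so no stated figure is refuted. It should be fixed because it governs what a null or small change would mean, but it is confined to one secondary end point and its analysis.

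**What to change.** 1. Redefine the secondary end point and the matching analysis sentence as change in IMR from immediately post-PCI (after the loading dose) to 6 months. State that it describes the maintenance phase and not the whole effect since randomization, which the 6-month comparison addresses.
2. Report the between-arm difference in the first IMR as an early on-treatment outcome.
3. Say what the baseline measurement before allocation is, and reconcile it with the schedule of two post-PCI IMRs.

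These are changes of wording and reporting; no new data are needed.

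A separate, inexpensive improvement concerns missing data. A standard repeated-measures ANOVA keeps only patients with both IMRs. With 20% loss that is about 96 of 120, although analyses are said to be by intention to treat. A linear mixed model (arm, time, arm × time) would use all randomized patients with at least one IMR, at the cost of a different model specification. It does not cure the timing fault: its arm-by-time term still measures change from the post-loading value.

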### Participants

Patients are eligible for enrollment if they are hospitalized for ACS with or without ST-segment elevation with an onset of symptoms during previous 24 h. All patients with ACS scheduled for PCI are eligible if they could understand the character and individual consequences of participation and provide written informed consent.

Exclusion criteria are (1) less than 20 years or more than 85 years old, (2) the presence of hemodynamic instability, (3) intolerance to antiplatelet drugs, (4) ineligible for coronary revascularization, (5) liver cirrhosis greater than or equal to Child class B, (6) decreased serum platelet level (< 100,000/uL), (7) need chronic oral anticoagulant therapy, (8) ACS in previous month, (9) a history of myocardial infarction in the target vessel-related territory, (10) a history of coronary artery bypass grafts, (11) renal dysfunction with creatinine > 3 mg/dL, (12) chronic total occlusion, (13) in-stent restenosis, (14) left main lesion, (15) contraindications to adenosine, (16) previous treatment with statins, (17) a life expectancy < 1 year, and (18) an inability to give informed consent. Complete listings of our inclusion and exclusion criteria are provided in Table 1.

**Table 1 Tab1:** Inclusion and exclusion criteria

Inclusion criteria
Hospitalized for potential ST-segment elevation or non-ST-segment elevation ACS, with onset during the previous 24 h, documented by cardiac ischemic symptoms due to atherosclerosis of ≥ 10 min’ duration at rest, male and female aged 20 to 85 years, not pregnant, and with informed consent And at least one of the following: 1) ST-segment changes on ECG indicating ischemia. ST-segment depression or transient elevation ≥ 1 mm in two or more two contiguous leads 2) Positive biomarker indicating myocardial necrosis. Troponin-I or CK-MB greater than the upper limit of normal or persistent ST-segment elevation ≥ 1 mm (not known to be preexisting or due to a coexisting disorder) in ≥ 2 contiguous leads or new LBBB plus primary PCI planned.
Exclusion criteria
1) Less than 20 years or more than 85 years old 2) The presence of hemodynamic instability 3) Intolerance to antiplatelet drugs 4) Ineligible for coronary revascularization 5) Liver cirrhosis greater than or equal to Child class B 6) Decreased serum platelet level (< 100,000/uL) 7) Need chronic oral anticoagulant therapy 8) Acute coronary syndrome in previous month 9) History of myocardial infarction in the target vessel-related territory 10) History of coronary artery bypass grafts 11) Renal dysfunction with creatinine > 3 mg/dL 12) Chronic total occlusion 13) In-stent restenosis 14) Left main lesion 15) Contraindications to adenosine 16) Previous treatment with statins 17) A life expectancy < 1 year 18) An inability to give informed consent.

*ACS* acute coronary syndrome, *ECG* electrocardiogram, *LBBB* left bundle branch block

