### Randomization

Random assignments are generated using the Excel spreadsheet software (Microsoft Corporation, Redmont, CA, USA). Eligible patients are randomly assigned in a 1:1 ratio to receive treatment with ticagrelor or clopidogrel. Randomization is performed by a person not involved in this study and kept concealed. Ticagrelor will be given in a loading dose of 180 mg followed by a dose of 90 mg twice daily. Patients in the clopidogrel group will receive 600 mg loading dose followed by a dose of 75 mg once daily. The randomized treatment will be continued for 6 months.

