### Sample Size

Sample size calculation was based on primary end point and primary analysis for the intention-to-treat population. Sample size was calculated using the study’s primary objective to detect a 30% relative difference in IMR measurements between ticagrelor and clopidogrel treatment with a power of 90% to demonstrate difference. On the basis of previous reports, we assumed the value of IMR after PCI to be approximately 35 U in ACS patients with clopidogrel treatment [12, 22, 23]. We expected that the relative difference in IMR measurement would be at least 30% when considering ACS patients. The assumed result of IMR after ticagrelor treatment was 25 U based on observations made in a pilot study performed to inform the design of the current trial. We adjusted the sample size considering an estimated follow-up loss rate of 20% with a two-sided level of significance *α* = 5% and a power of 1-β = 90%, resulting in 60 patients in each group to detect this difference with a two-sided Student’s *t* test. Therefore, a total of 120 patients will be randomized and included in this study.

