### Microvascular Dysfunction in ACS Patients

ACS is the leading cause of morbidity and mortality [2] in coronary artery disease. To predict clinical outcomes in patients with ACS, it is important to assess myocardial viability, for which microvascular function and integrity are the most important determinants. Coronary microcirculation which consists of resistance arterioles, capillaries, and small veins plays a major part in the delivery of blood and nutrients to the myocardium [43]. Microvascular dysfunction represents a predisposing factor for myocardial ischemia [44]. It is also an important prognostic factor of ACS [45, 46]. Despite the importance of microvascular coronary damage for prognosis, an accurate evaluation of microvascular function is challenging. Currently, no technique allows direct visualization of coronary microcirculation in vivo in humans. Most parameters for evaluating microvascular function rely on quantification of coronary blood flow. Among them, TIMI myocardial perfusion grade is a simple and useful clinical tool for microcirculation assessment. Even though ticagrelor has survival benefit, angiographic analysis from PLATO trial has shown that there is no significant difference in myocardial perfusion grade between ticagrelor and clopidogrel treatment groups [47]. Recently, IMR has been proposed and validated for assessing the status of microcirculation. Technological advance in measuring pressure and estimating coronary artery flow simultaneously using a single pressure-temperature sensor-tipped coronary wire has made it possible. IMR provides a quantitative measure of coronary microvasculature status. It is independently associated with LV function and infarct pathology [48, 49]. However, the protocol of the PLATO study did not involve IMR measurements or non-invasive tools such as positron emission tomography or magnetic resonance. Therefore, effects of ticagrelor maintain therapy on the prevention of microvascular dysfunction in ACS patients remain uncertain.

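### The primary 6-month IMR test is unadjusted for ACS presentation: it is valid, but it gives up precision to whatever extent IMR differs between STEMI, NSTEMI and unstable angina

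*Protocol article*

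**What the plan says.** All of this is in the protocol article.

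- **Participants:** eligibility covers patients "hospitalized for ACS with or without ST-segment elevation with an onset of symptoms during previous 24 h".
- **Table 2 (ticagrelor v clopidogrel, 60 per arm):** STEMI 18 v 20, NSTEMI 29 v 23, unstable angina 13 v 17, with p = 0.51 for diagnosis.
- **Microvascular Dysfunction in ACS Patients:** the article says of IMR, "It is independently associated with LV function and infarct pathology".
- **Statistical Analysis:** the aim is put as "The focus of this trial is to compare the efficacy by measuring IMR between the two study groups". The primary end point is tested with Student's t test, or otherwise with the Mann-Whitney U test. Neither has a covariate or stratum. Repeated-measures ANOVA is kept for change in IMR, which is a secondary end point. The only subgroup analysis named concerns quality of life.
- **Sample Size:** "we assumed the value of IMR after PCI to be approximately 35 U in ACS patients with clopidogrel treatment", and "The assumed result of IMR after ticagrelor treatment was 25 U", "with a power of 90% to demonstrate difference". No SD is given.

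**The concern.** The three presentations differ in how much myocardium has been injured. If IMR follows infarct pathology, as the article says, presentation may predict the primary end point, and it can be classified from data that precede study treatment. An analysis that leaves out such a factor counts the variation it explains as noise. The arm difference is then estimated with a wider confidence interval, and lower power, than the same patients could give.

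The primary test is a stated choice, so this is not a detail that the article merely leaves to another document. Enrolment is shown as complete, so the analysis is the remaining place to recover that precision.

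**Working it through.** **1. Reproducing the planned size.** Inputs from Sample Size: 35 v 25 U, so d = 10 U (28.6%; a full 30% would be 10.5 U), two-sided 5%, power 90%, loss 20%. The SD is not stated, so it has to be back-solved.

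n per arm = 2 × (1.960 + 1.282)² × SD² / d². With SD = 15: 2 × 10.51 × 225 / 100 = 47.3, rounded up to 48. Then 48 / 0.80 = 60, the planned figure. At 48 per arm, power is 90.4% by the normal approximation and 89.8% by the exact t distribution. SD = 15 U is therefore a working assumption that fits the plan; it is not a documented value.

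**2. Variance between presentations.** The Table 2 mix is p = 38/120, 52/120, 30/120 = 0.317, 0.433, 0.250. The article gives no IMR by presentation, so let D be an assumed gap between the highest and lowest type. Three patterns were used: STEMI v the rest, any infarction v unstable angina, and graded (D, D/2, 0).

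Between-type variance V = Σ p·m² − (Σ p·m)², where m is the type mean. Residual SD after adjustment = √(225 − V).

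Example, D = 10, STEMI v the rest: V = 0.317 × 0.683 × 100 = 21.6, which is 21.6 / 225 = 9.6% of the variance. Residual SD = √203.4 = 14.26. Standard error = 14.26 × √(2/48) = 2.91. Power = Φ(10/2.91 − 1.96) = 93.0%.

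Ranges over the three patterns, 48 evaluable per arm:

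| D (assumed) | V | Share of variance | Residual SD | Power, adjusted (unadjusted 90.4%) | CI narrower by (1 − residual SD/15) |
|---|---|---|---|---|---|
| 5 U | 3.5-5.4 | about 2% | 14.82-14.88 | 90.9-91.1% | about 1% |
| 10 U | 14.1-21.6 | 6-10% | 14.26-14.52 | 92.1-93.0% | 3-5% |
| 15 U | 31.6-48.7 | 14-22% | 13.28-13.91 | 94.1-95.8% | 7-11% |

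If 15 U is instead the SD within a presentation, the total SD is √(225 + V). Unadjusted power is then about 90% at D = 5, 88-89% at D = 10 and 84-86% at D = 15.

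**3. Effect of the observed imbalance.** The Table 2 p value reproduces: chi-squared = 2 × (1²/19 + 3²/26 + 2²/15) = 1.33 on 2 df, p = 0.51. The arm differences in proportion are −0.033 (STEMI), +0.100 (NSTEMI) and −0.067 (unstable angina). At D = 10 the expected shift in the contrast is −0.33 U (STEMI v the rest), +0.67 U (infarction v unstable angina) or +0.17 U (graded: −0.033 × 10 + 0.100 × 5). At D = 15 the largest is 1.0 U. The planned difference is 10 U.

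**4. Validity.** In 10,000 simulated trials with graded means and D = 15, the unadjusted t test rejected a true null 5.0% of the time.

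**5. What estimates by presentation could show.** Eighty per cent of 38, 52 and 30, halved, is about 15.2, 20.8 and 12 evaluable per arm. With SD 15, the 95% CI half-width 1.96 × 15 × √(2/n) is about 11, 9 and 12 U, as wide as the planned effect.

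**The case against.** The strongest reply is that the test is valid, the arms are matched and the size of any gain is conjecture. The article ties IMR to left ventricular function and infarct pathology. It does not say that IMR differs by diagnostic category, and least of all at 6 months. At a 5 U gap the gain is negligible, and nothing in the article favours a large gap. All of this stands, and it limits the point to efficiency.

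Four stronger readings are tempting, and the article does not support them.

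- **That randomization ignored presentation.** The Randomization section says "Eligible patients are randomly assigned in a 1:1 ratio to receive treatment with ticagrelor or clopidogrel" and names no strata, but it does not exclude them, and a condensed article may omit them. The point does not depend on this, since the stated test would ignore strata in any case.
- **That imbalance distorts the result.** Step 3 shows small shifts, and chance imbalance is already covered by the test's 5% error rate.
- **That presentation is the main prognostic variable.** Table 2 also holds ejection fraction, troponin-I and target vessel, and nothing ranks them. Presentation is one reasonable choice.
- **That the effect has been seen only in STEMI.** The cited loading-dose study was in STEMI, but the 25 U planning value comes from a pilot whose population is not stated. Nor could estimates by presentation settle whether an effect holds outside STEMI (step 5).

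It can also be said that adjusted analyses are often left to a statistical analysis plan. That covers sensitivity analyses, but the primary test is fixed in the article. Finally, the trial is open label and Table 2 already reports 6-month platelet results by arm, so a late change to the primary test could look data-driven. That is a fair warning, and the fix is conditional because of it.

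**Conclusion.** The point holds as a modest loss of efficiency. The primary comparison is valid and not materially affected by the observed imbalance, but it leaves any between-presentation variance in the error term when a factor already collected could remove it. With a total SD of 15 U and 48 evaluable per arm, the gain from adjusting is about 1 power point at D = 5 U, 2-3 at 10 U and 4-5 at 15 U. Both the SD and D are assumptions, so the true gain could be trivial or moderate. The case for acting rests on the low cost rather than on a demonstrated large benefit.

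**What to change.** If 6-month IMR has not yet been compared by arm, state in Statistical Analysis that the primary analysis is a linear model for 6-month IMR with arm and ACS presentation (STEMI, NSTEMI, unstable angina). If a rank test is kept, use a van Elteren test stratified by presentation. Classify presentation from pre-treatment data, since the split between NSTEMI and unstable angina may turn on troponin. Report the unadjusted result alongside.

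If IMR has already been compared by arm, keep the planned test as primary and report the adjusted model as a labelled sensitivity analysis.

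In either case, arm differences by presentation with 95% CIs may be shown, labelled descriptive. Eligibility need not change.

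The cost is two degrees of freedom and a sentence or two of text. No new data are needed, because the diagnosis is already in Table 2.
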